## 1.0 INTRODUCTION

The RESCUEicp trial protocol (Version 6, dated August 2015) describes the study design. The purpose of this Statistical Analysis Plan is to give a more detailed and comprehensive description of the methods for the analysis of the trial data, to avoid post hoc decisions that may affect the interpretation of the results of the statistical analysis.

## 2.0 RESCUEicp PROTOCOL

RESCUEicp is a randomised trial comparing optimal medical management with surgery (decompressive craniectomy) for the management of intra-cranial hypertension following head injury, refractory to first-line and second-line treatment measures (as per flowchart in page 15 of the protocol).

The study design is a two arm parallel group open randomised trial with a target total sample size of 400 patients (i.e. two groups of 200 patients) randomised to receive either optimal medical management or decompressive craniectomy.

### 2.1 Clinical Outcome Measures as Specified in the Trial Protocol (Version 6, dated August 2015)

1. The primary endpoint is the Extended Glasgow Outcome Scale (GOSE) at 6 months after randomisation.
2. The secondary endpoints are:
  - a. GOSE at 12 and 24 months after randomisation
  - b. Mortality at 6, 12 and 24 months after randomisation
  - c. SF-36 and SF-10 (below 16 years) questionnaires at 6, 12 and 24 months after randomisation
  - d. Glasgow Coma Scale (GCS) at discharge from neurosciences hospital
  - e. Assessment of ICP control
  - f. Time in intensive care
  - g. Time to discharge from the neurosciences hospital
  - h. Detailed health-economic analysis

Adverse events will also be reported.

### 2.2 Statistical Considerations

**Sample size determination:** The total number of patients will be 400 (200 in each arm of the study) for a 15% difference in outcome (increase in favourable outcome from 45% to 60%) (power 80%, 2-sided significance 0.05, loss to follow-up up to 15%).

**Randomisation:** Participants were randomly assigned to either surgical or medical therapy with a 1:1 allocation as per a computer generated randomisation schedule using permuted blocks of random sizes and stratified

by site. The block sizes were not disclosed in order to ensure concealment. Participants were randomised using a central telephone randomisation service. Allocation concealment was ensured, as the service did not release the randomisation code until the patient had reached stage 3 of the protocol.

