#### **4.2 Primary Outcome Measure**

The primary outcome measure will be the extended Glasgow Outcome Scale (GOSE) evaluated at six months. The main analysis will be an ordinal analysis based on the proportional odds model, with the result presented as the estimated common odds ratio with its corresponding 95% confidence interval and p-value. For this primary analysis the GOSE categories of upper good recovery and lower good recovery will be pooled since a blinded review of the distribution of GOSE revealed that there are too few patients in these categories to allow them to be analysed as separate categories.

The goodness-of-fit of this unadjusted proportional odds model will be tested. If the proportional odds model is rejected at the 5% significance level then that in itself will mean that there is evidence of a difference in the distribution of the GOSE scores between the two randomised groups, and the interpretation of the results will focus on describing the difference.

As a sensitivity analysis the proportion of patients achieving a 'favourable' outcome (defined as upper severe disability or better on the GOSE scale) will be compared between the randomised groups using a chi-squared test. The result will be presented as the estimated odds ratio with its corresponding 95% confidence interval and p-value, for comparison with the estimated common odds ratio, and also as the estimated absolute difference in the proportions with the corresponding 95% confidence interval.

Further exploratory analyses will examine the impact of covariate adjustment on the above analyses using ordinal and binary logistic regression respectively. Age, GCS motor score, pupils, and the last available pre-randomisation Marshall CT class will be taken as covariates. Three separate analyses will be undertaken as the GCS motor score and pupils have been recorded at three time points (initial, on arrival at the first hospital, on arrival at the neurosciences hospital). Mean/median value imputation will be used to allow the small proportion of patients with missing values for their baseline covariates to be included in these analyses.

The Glasgow Coma Scale sum at discharge will be analysed using the same ordinal methodology described above for the GOSE. If necessary, adjacent categories will be pooled if there are too few patients with any particular GCS.

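### Randomisation was stratified by site, but the primary, chi-squared and exploratory adjusted analyses ignore site; the cost is modest and depends on how far GOSE differs between sites

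*SAP*

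**What the plan says.** Section 2.2 of the SAP states that "Participants were randomly assigned to either surgical or medical therapy with a 1:1 allocation", and that the allocation list was a "computer generated randomisation schedule using permuted blocks of random sizes and stratified" by site. Site is the only stratification factor named.

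Section 4.2 defines the primary analysis: "The main analysis will be an ordinal analysis based on the proportional odds model". It is explicitly a treatment-only model: "The goodness-of-fit of this unadjusted proportional odds model will be tested". The sensitivity analysis compares the proportions with a favourable outcome by a chi-squared test with no strata. For the exploratory adjusted models, "Age, GCS motor score, pupils, and the last available pre-randomisation Marshall CT class will be taken as covariates"; site is not listed. GCS at discharge (section 4.2) and 12-month GOSE (section 4.3) take over the same methods.

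The nearest the SAP comes to site is section 4.4, where UK versus rest of the world is one of six subgroup factors tested by interaction. That is a two-level grouping of sites, not the stratification factor, and it plays no part in the primary test. The SAP gives no reason for leaving site out.

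**The concern.** Blocking within site forces the arms to be nearly equal in number at each site. Differences in outcome between sites then largely cancel out of the treatment comparison. A model without site does not know this: it still counts the between-site variation as noise in the standard error. If GOSE differs by site, confidence intervals come out wider than they need be, p-values are somewhat too large, and power is given up in a trial planned at 80%.

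Pre-specification is also at stake. Section 1.0 says the SAP exists to forestall decisions made after the data are seen. With no mention of site, whether and how to account for the one stratification factor stays open until after unblinding.

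**Working it through.** **Inputs from SAP section 2.2.** "The total number of patients will be 400 (200 in each arm of the study"); "increase in favourable outcome from 45% to 60"%; "power 80%, 2-sided significance 0.05, loss to follow-up up to 15"%. **Inputs assumed**, because the SAP does not give them: number and size of sites, block sizes, the ICC (written ρ) and the GOSE distribution.

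**1. The plan's sample size.** With a pooled variance under the null and no continuity correction,

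n per arm = [1.960·√(2×0.525×0.475) + 0.842·√(0.45×0.55 + 0.60×0.40)]² / 0.15² = 173.

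Allowing for 15% loss: 173/0.85 = 204 per arm, 408 in total; or 173×1.15 = 199 per arm, 398 in total. Both agree with 400 to within 3%. Site plays no part in this calculation.

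**2. Size of the test that ignores site.** With complete balance within site, the true null variance of the treatment difference is (1 − ρ) times the variance the unadjusted analysis assumes. The test statistic therefore has SD √(1 − ρ) instead of 1, and

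true size = 2·[1 − Φ(1.960/√(1 − ρ))].

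Example, ρ = 0.10: √0.90 = 0.949; 1.960/0.949 = 2.066; size 3.9%. Confidence intervals are too wide by a factor of 1/0.949 = 1.054.

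**3. Power, binary endpoint, 170 evaluable per arm (200×0.85).**

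(0.15 − 1.960·√(2×0.525×0.475/170)) / √((0.45×0.55 + 0.60×0.40)/170) = (0.15 − 0.106)/0.0536 = 0.819.

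This gives power of 79.4% at ρ = 0, and δ = 0.819 + 1.960 = 2.779. Power ignoring site is Φ((δ − 1.960)/√(1 − ρ)); power with site is Φ(δ/√(1 − ρ) − 1.960).

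| Assumed ρ | True size, site ignored | Power, site ignored | Power, site included | Points forgone |
|---|---|---|---|---|
| 0 | 5.0% | 79.4% | 79.4% | 0 |
| 0.02 | 4.8% | 79.6% | 80.2% | 0.6 |
| 0.05 | 4.4% | 80.0% | 81.4% | 1.4 |
| 0.10 | 3.9% | 80.6% | 83.4% | 2.8 |
| 0.20 | 2.8% | 82.0% | 87.4% | 5.4 |

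Power with site ignored rises slightly down the table. Blocking lowers the true variance whether or not the analysis uses it.

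**4. Simulation with the ordinal endpoint.** 400 patients; site-stratified blocks of 4 or 6; 15% random loss; an assumed seven-category GOSE; log odds ratio ln(0.60/0.40) − ln(0.45/0.55) = 0.606. The test without site was the rank score test, which is equivalent to the proportional odds score test. The test with site used ranks and fixed site effects. There were 6,000 runs for size and 3,000 for power, with Monte Carlo standard errors of about 0.3 and 0.6 points. Here the ICC is on the latent logistic scale; 0.10 corresponds to a between-site SD of 0.6.

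| Setting, latent ICC about 0.10 | Size without / with site | Power without / with site |
|---|---|---|
| 20 even sites | 3.9% / 5.1% | 84.4% / 86.6% |
| 20 uneven sites | 4.3% / 5.2% | 85.7% / 87.2% |
| 50 uneven sites | 4.6% / 5.3% | 86.2% / 86.0% |

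At latent ICC 0 to 0.02 there was no clear loss of size. In that range, with 50 uneven sites, fixed site effects cost power: 88.8% without site against 87.2% with it at ICC 0, and 88.9% against 87.2% at 0.02. A random site intercept was not itself simulated.

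**The case against.** The case for leaving the plan alone has several parts.

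- **The consequence is conditional.** A reader might infer that the primary test is conservative as a matter of fact. The documents do not support that: they give no site count, site sizes or between-site variation. The UK and rest-of-world recruitment makes differences plausible but does not establish them. This stands.
- **The stratification is not wasted.** A reader might infer that stratifying and then ignoring site throws the design away. It does not. The arms are still balanced within site and the true variance is still reduced; only the credit for that precision in the standard error is lost. This stands.
- **The odds ratio is not biased.** A reader might say that unmodelled site differences pull the common odds ratio towards 1. That is non-collapsibility: the unadjusted model estimates a marginal odds ratio and a model with site estimates a site-conditional one. Section 4.2 chose the unadjusted quantity openly. This stands.
- **Adjustment can cost power.** With many small sites, incomplete blocks shrink the benefit, and fixed effects lost 1 to 2 points when sites hardly differed. This stands against fixed effects. It does not apply in the same way to a random intercept, which approaches the unadjusted model as the between-site variance nears zero.
- **Geography is already covered.** Section 4.4 fits UK versus rest of the world, but only in a subgroup interaction model and at two levels. It does not account for the stratification in the primary test, so this part does not answer the point.

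**Conclusion.** The point holds as one of efficiency and pre-specification. The SAP randomises within site and then accounts for site in none of the analyses of section 4.2. The direction is certain in principle: if outcome varies by site, standard errors are too large and the size falls below 5%. The amount is not certain. For ICC 0.02 to 0.10 and near-complete balance within site, the size is about 4.8% down to 3.9%, and roughly 0.6 to 2.8 points of power are forgone. The effect is smaller with many uneven sites and negligible if sites barely differ. The figures rest on assumed site numbers, ICC and GOSE distribution.

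A reader might infer that the primary result would be unsound. It would not: type I error is not inflated, so a positive finding stays valid, and the unadjusted analysis remains a legitimate estimate of a marginal effect. This is a cheap improvement, not an error that undermines the trial.

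**What to change.** Before unblinding, amend section 4.2 as follows.

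- Include site as a random intercept in the primary proportional odds model. Do not use fixed effects for many small sites.
- Replace the plain chi-squared test for favourable outcome with a site-stratified Mantel-Haenszel analysis, pooling small sites by a rule written down in advance, for example by country.
- Keep the unadjusted proportional odds and chi-squared analyses as named sensitivity analyses, and say which model the goodness-of-fit test applies to.
- If the sponsor prefers the unadjusted primary analysis, name the site-accounting analysis as a sensitivity analysis instead and give the reason.

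The cost is SAP wording only; site is known for every patient because randomisation used it. There are three downsides. The primary odds ratio becomes site-conditional instead of marginal, which the report must say. Small sites need a pooling rule for the Mantel-Haenszel analysis. If between-site variation is near zero, little is gained.

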### **3.0 SCOPE OF THIS STATISTICAL ANALYSIS PLAN (SAP)**

This SAP covers the analysis of the clinical endpoints of the trial up until the 12 month assessment. The trial will be analysed and reported when the data to 12 months are available for analysis. Subsequent analysis of data from the 24 month assessment will be performed using the same statistical approach. A separate health-economic analysis plan will cover the analysis of the SF-36/SF-10 data and other health-economic endpoints.

### **4.0 DETAILED ANALYSIS PLAN**

#### **4.1 Analysis populations**

The analysis of all outcome (efficacy/effectiveness) measures and adverse events will be performed on the intention to treat (ITT) population, which will be defined as all randomised patients. The only exclusions will be those patients where the outcome data are not available and/or where consent was withdrawn.

A sensitivity analysis will be performed for the primary outcome measure using the per protocol (PP) population. The PP population will be defined as those patients included in the ITT population but excluding any patients where there had been a severe breach of protocol. Such exclusions will be agreed by the Trial Steering Committee ahead of the database being locked and unblinded, and will include, for example, patients where ICP was not monitored.

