#### **4.6 Adverse Events**

The number and type of adverse events that were observed during the trial will be summarised separately for each treatment group, based on all randomised patients.

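### Adverse events are summarised by randomised group only; if patients do not receive their allocated treatment, complications of craniectomy will be blurred between the arms, and a supplementary table by operation received would show it.

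*SAP*

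**What the plan says.** SAP section 4.1 sets a single population for effectiveness and safety alike: "The analysis of all outcome (efficacy/effectiveness) measures and adverse events will be performed on the intention to treat (ITT) population". The same sentence then fixes who belongs to it: "which will be defined as all randomised patients". Section 4.6 states the adverse-event rule again: counts and types of event "will be summarised separately for each treatment group, based on all randomised patients". No test, risk difference or confidence interval is named there.

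The only other population is per protocol, and its use is limited: "A sensitivity analysis will be performed for the primary outcome measure using the per protocol (PP) population". It is formed by "excluding any patients where there had been a severe breach of protocol". The one example given is a patient whose intracranial pressure was not monitored. The SAP does not say whether receiving the other arm's treatment counts as such a breach.

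Section 2.0 describes a "two arm parallel group open randomised trial with a target total sample size of 400 patients", comparing an operation with medical management in raised intracranial pressure that has already resisted earlier treatment. The SAP does not mention crossover, later craniectomy in the medical arm, or surgical-arm patients who are not operated on. It plans no count of any of these.

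**The concern.** Analysis by allocation answers the question of what happens under each assigned strategy. A reader of a table of complications usually also wants to know what the operation itself does. The two answers agree when everyone receives the allocated treatment and can part when some do not.

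The trial is open and one arm is a surgical procedure, so treatment received may differ from treatment allocated, and nothing in the SAP excludes this. If it happens, a wound infection or other complication of craniectomy in a medical-arm patient is listed under medical management, and unoperated patients lower the event count in the surgical column. When craniectomy raises the risk of complications, both effects pull the columns together, towards an appearance of less procedural harm. As no count of such patients is planned, a reader could not tell whether the table is affected at all, or by how much.

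This is a rule that the SAP states in two places, not a detail left to the protocol.

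**Working it through.** **The plan's own figures.** The SAP gives no adverse-event rate and no crossover rate, so there is no stated figure on this point to reproduce. Its one design calculation (section 2.2: "increase in favourable outcome from 45% to 60" per cent, 80% power, two-sided 0.05, up to 15% loss) does reproduce. A pooled-variance comparison of two proportions needs 173 per arm. Dividing by 0.85 gives 203.5, rounded up to 204 per arm or 408 in total, against the planned 400. That calculation does not bear on adverse events; only the arm size of 200 is used below.

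**Dilution formula.** Let

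- r1 = risk of a complication in a patient who has craniectomy,
- r0 = risk in a patient who does not,
- c = share of the medical arm that has craniectomy,
- d = share of the surgical arm that does not.

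Assume that risk depends only on treatment received. Then

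- medical column: (1 − c)·r0 + c·r1
- surgical column: (1 − d)·r1 + d·r0
- difference: (1 − c − d)·(r1 − r0)

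**Illustration.** All inputs here are assumptions: r1 = 15% and r0 = 5%, so the difference by treatment received is 10 points. The last column is 200 × c × 0.10.

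| c | d | Medical column | Surgical column | As-randomised difference | Share of 10 points | Extra medical-arm patients with an event, of 200 |
|---|---|---|---|---|---|---|
| 0% | 0% | 5.0% | 15.0% | 10.0 | 100% | 0 |
| 10% | 0% | 6.0% | 15.0% | 9.0 | 90% | 2 |
| 10% | 5% | 6.0% | 14.5% | 8.5 | 85% | 2 |
| 20% | 0% | 7.0% | 15.0% | 8.0 | 80% | 4 |
| 30% | 0% | 8.0% | 15.0% | 7.0 | 70% | 6 |

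For example, at c = 30% the medical column is 0.70 × 5% + 0.30 × 15% = 3.5% + 4.5% = 8.0%.

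**What the table does and does not show.** The proportional dilution is c + d by construction and does not depend on the assumed risks. The table therefore translates an assumed crossover rate; it does not estimate one. The direction (towards less apparent harm) holds for any c or d above zero, provided that r1 exceeds r0 and the assumption above holds. Patients who cross over are selected, and an operation done later may carry a different risk from one done at allocation. The factor would then no longer be exactly (1 − c − d).

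**The case against.** Reporting harms by allocation is legitimate. It puts harms and benefits on the same population and keeps the protection of randomisation. A comparison by treatment received gives that up: medical-arm patients who come to surgery differ from those who do not, and they must survive long enough to be operated on. This stands, and it is why the as-randomised table should remain the main one.

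A reader might infer several stronger things that the documents do not support.

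- **That the harm of surgery is understated.** This needs crossover, which the SAP neither mentions nor quantifies. The protocol, not reviewed here, may deal with it. With no crossover the dilution is zero.
- **That the understatement is some particular percentage.** Any such figure only restates the crossover rate that was put in, and it relies on risk depending solely on treatment received.
- **That the adverse-event table is the only evidence on harm.** Mortality is a listed endpoint (section 2.1), and GOSE is analysed as an ordinal scale at 6 and 12 months (sections 4.2 and 4.3). Both bear on the net harm of the surgical strategy. The table is, however, the only planned summary of complications as such.
- **That an estimated excess is biased, or that complications cannot be traced.** Section 4.6 plans a descriptive summary by type, not an effect estimate, so events specific to an operation may be recognisable in the medical column. They would still be counted there, and non-specific events such as infection could not be attributed from that table.

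What remains is narrower: the SAP fixes one presentation of adverse events, and if patients do not receive their allocation that presentation does not describe complications of the operation received.

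**Conclusion.** The point holds conditionally. Sections 4.1 and 4.6 tie adverse events to the randomised group, and the per-protocol analysis does not extend to them. If medical-arm patients have craniectomy, or surgical-arm patients do not, the apparent excess of surgical complications shrinks by the proportion c + d, assuming that craniectomy raises risk and that risk follows treatment received only. That is nothing at c = d = 0 and, with d = 0, 10% at c = 10% and 30% at c = 30%. These crossover values are illustrations, since the SAP gives none.

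The as-randomised summary is not an error and should not be replaced. This is a cheap improvement to how procedural harm is described. It has no bearing on the primary analysis.

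**What to change.** Keep the as-randomised table and add to section 4.6 words such as:

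> As a supplement, adverse events will be summarised by treatment received (decompressive craniectomy performed after randomisation, yes or no). For medical-arm patients who have a craniectomy, events before and after the operation will be shown separately. The number of patients in each arm who did not receive the allocated treatment will be reported. This summary is descriptive; the groups compared are not randomised.

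The split before and after the operation matters because a plain yes/no grouping would charge to surgery events that happened before it.

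The cost is one further table, from data that the trial should already hold (whether and when craniectomy was done, and the dates of events). The downside is that the added comparison is open to selection, so it must carry the descriptive label and no formal test. If every patient received the allocated treatment, the count of zero says so and the supplementary table adds nothing to the main one. Since section 1.0 gives the avoidance of decisions made after seeing the data as the SAP's purpose, the addition should be made before unblinding.

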#### **4.2 Primary Outcome Measure**

The primary outcome measure will be the extended Glasgow Outcome Scale (GOSE) evaluated at six months. The main analysis will be an ordinal analysis based on the proportional odds model, with the result presented as the estimated common odds ratio with its corresponding 95% confidence interval and p-value. For this primary analysis the GOSE categories of upper good recovery and lower good recovery will be pooled since a blinded review of the distribution of GOSE revealed that there are too few patients in these categories to allow them to be analysed as separate categories.

The goodness-of-fit of this unadjusted proportional odds model will be tested. If the proportional odds model is rejected at the 5% significance level then that in itself will mean that there is evidence of a difference in the distribution of the GOSE scores between the two randomised groups, and the interpretation of the results will focus on describing the difference.

As a sensitivity analysis the proportion of patients achieving a 'favourable' outcome (defined as upper severe disability or better on the GOSE scale) will be compared between the randomised groups using a chi-squared test. The result will be presented as the estimated odds ratio with its corresponding 95% confidence interval and p-value, for comparison with the estimated common odds ratio, and also as the estimated absolute difference in the proportions with the corresponding 95% confidence interval.

Further exploratory analyses will examine the impact of covariate adjustment on the above analyses using ordinal and binary logistic regression respectively. Age, GCS motor score, pupils, and the last available pre-randomisation Marshall CT class will be taken as covariates. Three separate analyses will be undertaken as the GCS motor score and pupils have been recorded at three time points (initial, on arrival at the first hospital, on arrival at the neurosciences hospital). Mean/median value imputation will be used to allow the small proportion of patients with missing values for their baseline covariates to be included in these analyses.

The Glasgow Coma Scale sum at discharge will be analysed using the same ordinal methodology described above for the GOSE. If necessary, adjacent categories will be pooled if there are too few patients with any particular GCS.

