### **4.3 Secondary Outcome Measures**

ICP control

The following will be presented:

- a. Mean ICP after randomisation (in mmHg)
- b. Number of hours with ICP > 25 mmHg after randomisation
- c. Intracranial hypertension index. This is the number of end-hourly measures of ICP > 20 mmHg divided by the total number of measurements, multiplied by 100. The number of end-hourly measures of ICP > 25 mmHg divided by the total number of measurements, multiplied by 100 will also be presented.
- d. Cerebral hypoperfusion index. This is the number of observations of cerebral perfusion pressure of less than 60 mm Hg divided by the total number of measurements, multiplied by 100. Cerebral perfusion pressure is the mean arterial pressure minus the intracranial pressure.

Duration of intensive care and duration of neurosurgical unit stay will be analysed using survival techniques, with Kaplan-Meier survival estimates and logrank tests to compare optimal medical management with surgery (decompressive craniectomy). Results will be presented as unadjusted hazard ratios with corresponding 95% confidence intervals and p-values.

GOSE at 12 months will be analysed using the same statistical methods set out above for the GOSE at 6 months.

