#### **4.5 Adjustment for multiplicity**

Adjustment for multiplicity is considered unnecessary since the trial has a single pre-specified primary outcome measure. The secondary outcomes are exploratory and the results will only be interpreted as supportive evidence related to the primary outcome.

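### Section 4.2 gives the primary outcome two unadjusted 5% tests; if rejection by either counts as a finding of a difference, the false-positive rate is about 10%, not 5%

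*SAP*

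**What the plan says.** Section 4.2 of the SAP names one main analysis of GOSE at six months: an ordinal analysis under proportional odds, "with the result presented as the estimated common odds ratio with its corresponding 95% confidence interval and p-value". It pools the two good-recovery categories. It then requires a goodness-of-fit test of the unadjusted model and says that if the model is "rejected at the 5% significance level then that in itself will mean that there is evidence of a difference" in the GOSE distribution between the groups. Interpretation is then to concentrate on describing that difference.

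The only design-level statement of the significance level is in section 2.2: "power 80%, 2-sided significance 0.05, loss to follow-up up to 15" per cent. Section 4.5 disposes of multiplicity in one sentence: "Adjustment for multiplicity is considered unnecessary since the trial has a single pre-specified primary outcome measure". It adds that secondary outcomes are exploratory and supportive.

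The same approach is carried to other outcomes. Section 4.3 says "GOSE at 12 months will be analysed using the same statistical methods set out above for the GOSE at 6 months", and section 4.2 applies the same ordinal method to GCS at discharge.

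No section divides the 5% between the two tests, and none says that the fit test cannot support a finding.

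**The concern.** The phrase about rejection counting in itself makes the fit test more than a model check. It becomes a free-standing basis for saying that the arms differ on the primary outcome, whatever the common odds ratio shows. One outcome then has two routes to a declared difference, each at 5%. The reason given in 4.5 concerns the number of outcomes, whereas the multiplicity here comes from the number of tests of one outcome.

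Two things are at stake. First, the two-sided 0.05 of section 2.2 would not describe the chance of a false finding on the primary outcome. Second, the fit test has no direction. A trial with a common odds ratio near 1 could be reported as showing a difference without showing that either arm is better, and the SAP has no decision rule for that case.

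**Working it through.** **Inputs from the SAP**
- Two-sided 0.05, 80% power, up to 15% loss, 45% versus 60% favourable, 400 patients in two arms of 200, 1:1 allocation (section 2.2).
- Common-odds-ratio test with 95% interval and p-value; fit test at 5%; top two categories pooled (section 4.2).

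**Assumptions**
- GOSE has 8 levels, so pooling leaves 7. The odds-ratio test then has 1 df and the fit test 5 df.
- The odds-ratio p-value is judged at 0.05. Section 4.2 does not say so; this comes from section 2.2 and the 95% interval.
- The fit test is unnamed, so Pearson and likelihood-ratio forms were both tried.
- The outcome distributions simulated are assumed.

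**Step 1. The plan's own figure.** With p̄ = 0.525,

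n per arm = [1.96·√(2·0.525·0.475) + 0.842·√(0.45·0.55 + 0.60·0.40)]² / 0.15² = 172.8, so 173.

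Allowing for 15% loss, 173/0.85 = 203.5, so 204 per arm or 408 in total. The looser 173 × 1.15 = 199 per arm gives about 400. With 170 per arm followed up (200 × 0.85), power is 79.4%. The stated 400 is reproduced. It assumes one test at two-sided 0.05.

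**Step 2. False-positive rate of the two routes.** If the arms have identical GOSE distributions, proportional odds holds exactly with an odds ratio of 1. Each test then rejects about 5% of the time, and the two are asymptotically independent:

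P(either rejects) = 1 − 0.95 × 0.95 = 0.0975.

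Order does not matter. Testing fit first, and the odds ratio only if fit is not rejected, gives 0.05 + 0.95 × 0.05 = 0.0975. Without independence the upper bound is 0.05 + 0.05 = 0.10.

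**Step 3. Simulation with no treatment effect.** There were 10,000 trials per row, with a Wald test of the odds ratio. Fit and either-test results are shown as Pearson / likelihood-ratio.

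| Assumed distribution, 7 categories (%) | Per arm | Odds ratio | Fit | Either |
|---|---|---|---|---|
| 25, 5, 18, 12, 15, 13, 12 | 170 | 5.1% | 5.4 / 5.8% | 10.2 / 10.6% |
| same | 200 | 5.0% | 4.9 / 5.2% | 9.6 / 10.0% |
| 40, 5, 20, 10, 12, 8, 5 | 200 | 5.0% | 5.4 / 6.0% | 10.2 / 10.8% |
| equal | 200 | 5.3% | 4.8 / 5.1% | 9.8 / 10.1% |

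The correlation between the odds-ratio and Pearson rejections lay between −0.006 and 0.007. A separate run (170 per arm, two assumed distributions, 40,000 trials each) gave 5.0% for the odds ratio, 5.0% to 5.1% for fit, and 9.8% to 9.9% for either.

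**Step 4. Error rate under the remedies.**
- Odds-ratio test alone at 5%: 5% (simulated 5.0% to 5.3%).
- Each route at 2.5%: 1 − 0.975² = 0.0494 (simulated 4.8% to 4.9%).

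**Step 5. Power under the remedies.** The design effect as an odds ratio is (0.60/0.40)/(0.45/0.55) = 1.83, with log 0.606. With 400 × 0.85 = 340 patients, 1:1 allocation and true proportional odds, the information is V = (340/12)(1 − Σm³), where m is the mean category proportion over the two arms. Taking the first distribution above for the control arm, V = 27.6 and the noncentrality is 0.606 × √27.6 = 3.18.
- At 5%: Φ(3.18 − 1.96) = 89%.
- At 2.5%: Φ(3.18 − 2.24) = 83%.
- A single joint 6-df test at 5%, noncentrality 3.18² = 10.1: 65%.

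Over all three assumed distributions these become 88% to 89%, 82% to 83%, and 64% to 65%.

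**The case against.** The strongest reply is that the sentence in 4.2 is logically true. Identical distributions satisfy proportional odds with an odds ratio of 1, so rejecting the fit does imply that the distributions differ. That stands for the fit test taken alone at 5%. It does not justify adding that test, unadjusted, to another 5% test of the same outcome.

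A second reply is that 4.2 names only one main analysis, and that on rejection of fit it promises a description and no verdict of superiority. On that reading the odds-ratio test keeps its 5% level. The reading is tenable, but no section secures it. The text gives evidence of a difference on the primary outcome as the meaning of the rejection, and it gives no decision rule. What survives of this reply is that the 10% is conditional on treating either rejection as a finding.

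A reader might go further and infer a 10% chance of falsely declaring surgery or medical management better. The SAP does not support that, because the fit test does not point to either arm and 4.2 does not claim that it does.

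A reader might also extend the error-rate charge to 12-month GOSE and GCS at discharge, which inherit the method. Section 4.5 calls secondary outcomes exploratory, so no 5% claim attaches to them.

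Finally, making the fit test purely descriptive has a real drawback. If the cumulative odds ratios cross, the common odds ratio can be near 1 while the arms truly differ. That cost belongs with the fix.

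**Conclusion.** The point holds in conditional form. As written, 4.2 leaves two unadjusted 5% tests of the primary outcome. If rejection by either is taken as a finding of a difference, the false-positive rate is about 9.75% (simulated 9.6% to 10.8%), roughly double the 0.05 of section 2.2. The rationale in 4.5 does not answer this.

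The asymptotic figure needs only that each test is run at 5% and that the two are independent under no effect. It does not depend on the number of categories or on the form of the fit test. The simulated range does rest on the assumed 7 categories and distributions. For the secondary outcomes the matter is one of consistent interpretation only.

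**What to change.** **Preferred.** State in 4.2 that the common-odds-ratio test at two-sided 5% is the sole confirmatory test of the primary outcome. Add that rejection of fit only directs how the difference is described, for example by category-specific or cumulative odds ratios, and is not a separate positive result. Reword the sentence about rejection counting in itself to say this. The odds-ratio test loses no power. The price is that a pure shape difference, with a common odds ratio near 1, can only be described.

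**Alternative, if the sponsor wants rejection of fit to count.** Test each route at 2.5%, for a combined rate of about 4.9%. Odds-ratio power falls from about 89% to 82–83% at an odds ratio of 1.83 with 340 patients. The SAP should then also say that a rejection by the fit test alone does not show which arm is better.

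A single joint 6-df test would also hold 5%, but it is not recommended: its power in the same setting is about 64–65%.

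Amend the rationale in 4.5 to match the choice, so that it addresses the two tests as well as the single outcome. Give the fit test the same interpretive role for 12-month GOSE and GCS at discharge, for consistency. All of this is SAP wording, and it should be settled before unblinding.
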